**Methods:**

Within five years, approximately 5000 CCS will be invited to visit one of the 10 LTFU centers in Germany. Study participants are either contacted by the German Childhood Cancer Registry (GCCR), transitioned from the local pediatric oncology care unit, or recruited via media. They are assigned to one of three different risk groups based on an evidence-based risk stratification and receive standardized multidisciplinary follow-up care.

Primary outcomes are satisfaction with the LTFU care offer as well as degree of health-related self-efficacy expectation. They will be assessed at two time points. A scientific evaluation of the implemented LTFU care will be enabled by a waitlist control group. The harmonized outcome data are documented in a standardized database.

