### Statistical analysis

With regard to the pre-post-comparison after three years in phase 1, small to medium effect sizes can be assumed based on the literature. However, it must be considered that the largest effects are expected in the stratum (i.e. in the group) of patients with high and medium risk, and smaller effects in the stratum of patients with low risk. Therefore, the two strata with high and medium risk are first tested equally, and the stratum with low risk is tested separately in a hierarchical manner. In order to comply with the global significance level of 5% when testing initially two strata and two primary endpoints, a local significance level of 1.25% is used in each case. With a power of 90%, a sample of *n* = 370 per stratum is sufficient to detect an effect of delta = 0.2. This number is achieved in the strata with medium and high risk if 1000 patients are included per year, of whom 400 patients fall into the group with high and medium risk respectively and of whom about 95% participate in the study. Patients enrolled in the first year will be surveyed in the fourth year with a 3-year follow-up, at which time the primary outcome criteria will be measured.

Regarding the parallel group comparison in phase 2, the sample size is estimated so that an effect of delta = 0.25 can be detected with a power of 80% for both primary endpoints. 310 patients per risk group (each in the intervention and control group), i.e. 620 patients in one stratum, must therefore be included in the study. If the participation rates in the first two years of the study (captured in an interim evaluation after two years) already indicate that the number of probands for the summative evaluation will be too low despite the recruitment measures described, only one single endpoint can be analyzed in the final evaluation. In this case, 255 patients per group in one stratum, i.e. 510 patients in one stratum in total, would be included in the study.

In both phases, the primary analyses will be performed by estimating generalized linear models including primary oncological disease, sex, and time since treatment as covariables. Details will be fixed in the statistical analysis plan.

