## Discussion

As many CCS are affected by chronic health conditions later in life that may occur as a consequence of former cancer treatment exposure, life-long LTFU care is essential to ensure timely diagnosis and treatment of possible late effects [2, 18]. Several guidelines and expert groups propose a center-based care model with multidisciplinary LTFU teams as central coordinator of LTFU care [19–21]. These centers offer experience and knowledge about late effects and provide risk-adapted surveillance examinations. Additionally, information about late effects of cancer treatment as well as advice on a healthy lifestyle as a preventive measure can be integrated in the consultations [6]. However, only a few centers in Europe offer LTFU care for adult CCS so that continuation of care after transition from pediatric to adult care unit is often interrupted [19]. Consequently, the majority of adult CCS in Germany are currently not in specialized LTFU care as they have either never been informed about their potential risk to develop late effects (being treated in the 1980s, 1990s or even earlier) or finished LTFU care after end of surveillance in the pediatric oncology department as no corresponding specialized adult centered care unit was available.

In order to improve LTFU care for adult survivors of childhood cancer in Germany, the LE-Na study was developed aiming to include 5000 CCS that have not received LTFU care yet. Therefore, national LTFU care structures have been established prior to study initiation at ten university hospitals providing standardized and risk-stratified LTFU care for this patient cohort. It is intended to expand this network of clinics. Standardized and risk-stratified LTFU care, as described in this manuscript, is currently already being set up in three additional clinics. Evaluation of this care offer, looking at different endpoints such as satisfaction with the LTFU care offer as well as degree of health-related self-efficacy expectation, will be used to facilitate adaptions of care structures to patients’ needs.

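### Phase 2 states numbers to be included that equal the requirement with no loss, and phase 1 leaves almost no room for loss over three years in the cohort it counts

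*Protocol article*

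**What the plan says.** All sample-size statements are in the Statistical analysis section of the protocol article.

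- **Phase 1** (pre-post comparison, questionnaires at the first consultation and three years later). With two strata and two endpoints, "a local significance level of 1.25% is used in each case". At 90% power, "370 per stratum is sufficient to detect an effect of delta = 0.2". The text says this number is reached in the medium- and high-risk strata, given an annual intake of 1000. The split and uptake it assumes are these: "of whom 400 patients fall into the group with high and medium risk respectively and of whom about 95% participate in the study". It adds that first-year enrolees are surveyed in the fourth year.
- **Phase 2** (randomised waiting-list comparison, web questionnaires at the start and after 12 months). The target is 80% power for a difference of 0.25 on both primary endpoints. This is given as 310 per arm, and "620 patients in one stratum, must therefore be included in the study". If participation in the first two years looks too low, one endpoint is dropped and 255 per arm (510 per stratum) would be included.

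Neither phase has a stated retention or questionnaire-return rate, and neither calculation shows an allowance for loss.

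**The concern.** A patient who joins but does not return the later questionnaire contributes no pre-post pair in phase 1 and no 12-month outcome in phase 2. The number that governs power is therefore the number with both assessments. The article uses the language of inclusion and participation for figures that look like completer requirements.

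Phase 2 matters more. The Study design section says this comparison was developed with health economists to support full cost coverage by the health insurers. Its follow-up is a web questionnaire a year later, and the waiting arm has had no clinic visit by then. If the real power is nearer 70% than 80%, a null result could be read as evidence against the care model when the comparison was simply too small.

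**Working it through.** **Inputs from the article.** Phase 1: standardised effect 0.2, local level 1.25%, power 90%, n = 370 per stratum, 1000 per year, 400 per stratum, 95% participation. Phase 2: effect 0.25, power 80%, 310 per arm (two endpoints) or 255 per arm (one endpoint).

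**Inferred.** Two-sided testing is not stated. In phase 1, one-sided 1.25% gives only 311 to 313, so two-sided is taken. The phase 2 level is not stated either; 2.5% for two endpoints and 5% for one are taken because they reproduce 310 and 255.

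**Assumed.** Loss rates of 5% to 30%, because the article gives none.

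**Step 1: reproduce the phase 2 figures.** n per arm = 2 × ((z for level + z for power) / delta)².

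- Two endpoints: 2 × ((2.241 + 0.842) / 0.25)² ≈ 304.2, so 305; the t-test gives 306. Stated: 310. The margin is 1 − 306/310 = 1.3%.
- One endpoint: 2 × ((1.960 + 0.842) / 0.25)² ≈ 251.2, so 252; the t-test gives 253. Stated: 255. The margin is 1 − 253/255 = 0.8%.

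Both figures are the formula value, slightly rounded up, with no inflation for loss.

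**Step 2: phase 2 power after loss** (two-sample t-test, noncentral t).

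| Loss at 12 months | From 310 per arm: n, power | From 255 per arm: n, power |
|---|---|---|
| 5% | 294, 78.3% | 242, 78.4% |
| 10% | 279, 75.9% | 229, 76.1% |
| 20% | 248, 70.4% | 204, 71.2% |
| 30% | 217, 63.9% | 178, 65.3% |

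**Step 3: reproduce the phase 1 figure.** n = ((z for level + z for power) / delta)² = ((2.498 + 1.282) / 0.2)² ≈ 357.1, so 358; the paired t-test gives 361. The stated 370 is within 3% of 361, so it is a number of completed pairs.

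**Step 4: what the accrual sentence supplies.** 400 × 0.95 = 380 participants per stratum from one year of inclusion.

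- Loss that still leaves 370 pairs: 1 − 370/380 = 2.6%.
- Loss that still leaves 90% power: 1 − 361/380 = 5.0%.

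**Step 5: phase 1 power after loss, from 380** (paired t-test, noncentral t).

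| Loss over three years | Pairs | Power |
|---|---|---|
| 0% | 380 | 91.7% |
| 5% | 361 | 90.1% |
| 10% | 342 | 88.2% |
| 20% | 304 | 83.4% |
| 30% | 266 | 77.2% |

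**Step 6: later phase 1 enrolees.** Data collection runs to the end of 2027, so anyone enrolled by the end of 2024 can reach three years.

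- Two full years at the planned rate: 2 × 380 = 760 per stratum, which keeps 370 pairs with up to 1 − 370/760 = 51% loss.
- From the October 2023 start given in the Results section, 15 months at that rate: 1.25 × 380 = 475, which tolerates 1 − 370/475 = 22%.

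Both figures assume that the planned rate is met. The Results section dates registry recruitment only from February 2024.

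**The case against.** **Phase 1.** The strongest reply concerns the size of the gap. The stated 370 already exceeds the 361 needed, so about 5% loss leaves 90% power intact and 10% loss costs under two points. Nothing in the article restricts the primary analysis to first-year enrolees, and step 6 shows that later ones could cover substantial loss. Retention is also supported: risk groups 2 and 3 can answer at a regular visit, and consent records a preferred contact route for the three-year questionnaire. These points stand. A reader might infer that phase 1 cannot deliver its stated power under any realistic loss; the document does not support that. What remains is that the article says the number is achieved, on one year's cohort, without any retention figure.

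The 95% could also be meant as participation in the three-year evaluation. The wording does not say so, and on that reading nothing is left for people who decline to take part.

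**Phase 2.** The plan has a fallback to one endpoint. With 310 per arm enrolled and one endpoint tested, 1 − 255/310 = 18% could be lost before falling below 255. This is only partial relief. The fallback lowers the number to be included to 255, which is itself uninflated. Its trigger is participation in the first two years, before phase 2 runs in years 3 and 4, so it cannot respond to 12-month loss in phase 2.

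**Deferral to the SAP.** The article leaves details of the analysis to the SAP, and a condensed article may omit an attrition assumption. But it prints specific numbers to be included and a claim that the phase 1 number is reached, and those can be checked as they stand. Covariate adjustment might recover some power; no figure is given for it.

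**The 5000.** A reader might also infer a conflict over accrual, because the Abstract has "approximately 5000 CCS will be invited to visit one of the 10 LTFU centers in Germany" and the Discussion speaks of "aiming to include 5000 CCS that have not received LTFU care yet". The Study population section separates 5000 survivors brought into care by three routes from 5000 registry invitations, and the 1000 per year is an explicit condition. It adds nothing to this point.

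**Conclusion.** The concern holds mainly for phase 2. As written, 310 and 255 per arm are completer numbers presented as numbers to include, and the stated 80% power is already missed at 5% loss (78%), falling to 76% at 10% and 70% to 71% at 20%. For phase 1 it holds in a weaker form: on the first-year cohort, power is 88%, 83% or 77% at 10%, 20% or 30% loss, unless later enrolees with a three-year assessment are counted.

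The arithmetic printed in the article is not wrong; what is missing is the step from participants to completed assessments. The sizes rest on two-sided tests, on the inferred phase 2 levels, on effects standardised as the formulas require, and on assumed loss rates. Severity: should-fix.

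**What to change.** 1. State that 370 per stratum (phase 1) and 310 or 255 per arm (phase 2) are numbers with both assessments.
2. State an assumed retention for each phase, with its basis, and restate the expected power. For illustration only: 20% loss from 310 per arm leaves 248 and 70% power; 20% loss from 380 per stratum leaves 304 pairs and 83% power.
3. For phase 1, say whether participants enrolled after the first year who reach three years by the end of 2027 enter the primary analysis, and base the expected number of pairs on that.

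The cost is wording and a less favourable stated power, with no change to design or analysis and no extra patients. Holding 80% power in phase 2 by enrolling more would be a separate decision: 310/0.9 = 345 per arm at 10% loss, or 310/0.8 = 388 at 20%.

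### The phase 2 fallback gives up one primary endpoint unnecessarily: 255 per arm also supports a fixed-sequence test of both

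*Protocol article*

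**What the plan says.** The abstract names two primary outcomes side by side: "Primary outcomes are satisfaction with the LTFU care offer as well as degree of health-related self-efficacy expectation". Table 1 lists both as primary without ranking them, and gives two instruments for self-efficacy, GSE and HCSE.

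For phase 2, the Statistical analysis section says that "the sample size is estimated so that an effect of delta = 0.25 can be detected" "with a power of 80% for both primary endpoints". This leads to "310 patients per risk group (each in the intervention and control group), i.e. 620 patients in one stratum". The contingency follows: if participation in the first two years, captured in an interim evaluation, points to too few participants, "only one single endpoint can be analyzed in the final evaluation". The size then changes: "In this case, 255 patients per group in one stratum, i.e. 510 patients in one stratum in total, would be included in the study".

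The section ends with a general deferral of details to the statistical analysis plan, directly after the sentence on models and covariables.

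**The concern.** The fallback treats loss of an endpoint as the unavoidable price of a smaller sample. That holds only if the two endpoints must share the significance level in equal parts. If they are tested in order, each can use the full level, and the smaller sample serves both.

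The Study design section presents phase 2 as the randomised evidence meant to support full cost coverage by the health insurers. Under the fallback, one of the two outcomes chosen to make that case has no confirmatory test at all. Phase 2 participants answer the questionnaires at baseline and at 12 months, and nothing in the article suggests that either outcome would stop being collected.

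**Working it through.** **Inputs.** From Statistical analysis: standardised effect 0.25 (SD = 1), power 80%, equal arms of 310 (main plan) or 255 (fallback). Assumed: two-sided 5% in one stratum, because the section states a 5% global level only for phase 1; correlation between the two test statistics from 0 to 0.8, because the article gives none. No dropout allowance is stated for phase 2, so 255 is taken as the number analysed.

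**Step 1: reproduce the stated sizes.** Per arm, n = 2(z_α/2 + z_power)² / δ².

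- One endpoint at 5%: 2 × (1.960 + 0.842)² / 0.0625 = 251.2, so 252 (t-test 253). Stated: 255.
- Two endpoints at 2.5% each: 2 × (2.241 + 0.842)² / 0.0625 = 304.2, so 305 (t-test 306). Stated: 310.

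Both agree within 2%. The difference of 310 − 255 = 55 per arm is therefore explained by alpha alone: 5% undivided against 2.5% each.

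**Step 2: power at 255 per arm.** Power = Φ(δ / √(2/n) − z_α/2), with 0.25 / √(2/255) = 2.823.

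- At 5%: Φ(2.823 − 1.960) = Φ(0.863) = 80.6% (t-test 80.4%).
- At 2.5%: Φ(2.823 − 2.241) = Φ(0.582) = 72.0% (t-test 71.7%).

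Splitting alpha at 255 would thus fall short of 80%, which explains why the plan turns to one endpoint.

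**Step 3: fixed sequence at 255 per arm.** Test the first endpoint at 5%. Test the second at 5% only if the first is significant.

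- Family-wise error: if the first null hypothesis is true, any false claim requires its rejection, which has probability at most 5%. If only the second is true, a false claim requires rejecting the second, again at most 5%. The family-wise rate stays at 5%.
- Power for the first endpoint: 80.6%, the same as in the single-endpoint fallback.
- Power to show both, with delta 0.25 on each (bivariate normal):

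| Correlation | Both shown |
|---|---|
| 0 | 65% (0.806² = 0.649) |
| 0.3 | 67.5% |
| 0.5 | 69.5% |
| 0.7 | 72% |
| 0.8 | 74% |

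**Step 4: compare with the main plan.** At 310 per arm and 2.5% each, power is 80.8% per endpoint and 65.3% to 69.8% for both at correlation 0 to 0.5. The sequence at 255 gives nearly the same chance of showing both (64.9% to 69.5%). What the larger sample buys is the chance to claim either endpoint on its own: at least one is shown in 96.3% to 91.8% of trials over the same correlations, against 80.6% for the sequence.

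**The case against.** **A single endpoint is a valid design.** One endpoint, named in advance and tested at 5%, is not an error, and the unseen SAP may name it. Both statements stand, so the missing name is not the point here. What remains is that the article itself fixes a one-endpoint rule together with its sample size, and a better rule is available at that size. The sequence also requires a leading endpoint, so it asks for no commitment that a valid single-endpoint fallback would not need.

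**A stronger reading is tempting.** Because the retained endpoint is not named, a reader might infer that it could be picked once results are in hand. Such a choice would raise the false-positive rate to between 7.8% and 9.8% (correlation 0.8 down to 0). This is hypothetical. The trigger is participation, not effects. The evaluation comes after two years, whereas phase 2 runs in study years 3 and 4 with its second questionnaire after 12 months, so no phase 2 follow-up outcome exists when the fallback is decided. The phrase about the final evaluation says where the analysis takes place, not when the choice is made.

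**Not everything is lost under the fallback.** Data on the other outcome would still be collected and could be reported descriptively. That is correct; the loss is the confirmatory test.

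**The strata are ambiguous.** If two strata shared the 5%, the first endpoint at 255 per arm would have 72.0% power. This is a fair limit, but it affects the plan's own fallback equally and does not change the comparison.

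**Conclusion.** The fallback is more restrictive than its sample size requires. With 255 per arm, a fixed sequence gives the leading endpoint the same power of about 80%, keeps the family-wise error at 5%, and adds a valid test of the second endpoint, with about 65% to 74% power to show both. Provided that the leading endpoint is the one the fallback would have kept, nothing is lost by the change.

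This rests on a two-sided 5% level in one stratum (inferred from the stated sizes), delta 0.25 on both endpoints, an assumed correlation of 0 to 0.8, and 255 analysable patients per arm. It matters only if the fallback is triggered. It is an avoidable loss of information, not an invalid analysis, and the article gives no ground for a finding that the 5% level is breached.

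**What to change.** Replace the single-endpoint fallback with wording such as: *If participation is too low, 255 patients per group are included and both primary endpoints are tested in a fixed sequence, each at the two-sided 5% level in the one stratum analysed; the second is tested only if the first is significant.*

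State the order of the endpoints, and whether GSE or HCSE is the test variable for self-efficacy. Do this no later than the two-year interim evaluation and before any phase 2 outcomes by arm are seen. State the phase 2 alpha and the number of strata sharing it, so that the 255 can be checked. If the SAP already names the endpoint to be kept, that endpoint can lead the sequence.

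The cost is a few sentences in the protocol or SAP, with no added patients or data collection. The downside is that the sponsor must commit to an order, and the second endpoint cannot be claimed if the first fails.

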**Secondary outcomes**	
Implementation of guideline recommendations in specialized LTFU care centers	Operationalized as use of risk stratification and guideline recommendations by the study centers (annual survey)
Health related quality of life	EORTC QLQ C30
Incidence and prevalence of late effects	

^a^Instructions of the PSQ-18 and GSE have been slightly adapted to set the questionnaire into the context of LTFU after childhood cancer

Additionally, during study year 3 and 4 (phase 2), the implementation of LTFU care will be tested randomized using a waiting list control group, again, regarding the primary endpoints. This intervention was developed together with health economists in order to provide evidence for the benefit of standardized LTFU care that can be used to obtain full cost coverage by the health insurance companies. All potential study participants in this phase are contacted by the GCCR and are asked to participate in this randomized trial. Randomization is carried out by the GCCR that defines a group of potential participants that is stratified according to gender, cancer diagnosis, time since end of therapy and residency. Participants of the intervention group in phase 2 receive an invitation to visit the LTFU clinic within the following three months. They complete the questionnaires web-based before their first visit as well as after 12 months. Participants of the waiting control group receive an invitation to complete the questionnaires web-based initially and a second time after 12 months. After filling out the questionnaire at these two time points, the waiting control group visits the LTFU clinic (one year later than the intervention group) and receives the same standardized LTFU care.

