### Ethics approval and consent to participate

This study was approved by the ethics committee of the University of Lübeck (registration number 2022–647). Given informed consent is required to participate in the study.

Potential participants in phase 1 will be informed about the study prior to the initial consultation and, if interested, asked to give their written informed consent by the physician in charge as soon as they visit the LTFU clinic. Participants document on the informed consent form whether they want to be contacted via e-mail or mail to fill out the second questionnaire after three years if they do not attend the clinic at this time during their regular LTFU.

Potential participants of the waiting list control design (phase 2), will be invited to take part in the study via mail by the GCCR. The invitation contains information about the random allocation to the intervention or the waiting control group and explains that the randomisation result will be communicated at a later date. If CCS are interested to participate, they contact a LTFU clinic of their choice by telephone. Each LTFU center has an ID list of all CCS contacted by the GCCR along with the randomisation results. The respective LTFU center coordinator asks the CCS if they confirm study participation in the randomization trial. If the CCS agrees, the LTFU center coordinator records the CCS's contact data and informs the CCS afterwards by email about the randomisation result and a proposed date for the first LTFU appointment. The participant also receives a link to a portal (e.g. SoSci Survey) to fill in the questionnaires web-based before the first consultation in the clinic. Prior to answering study items, participants have to read the study information and give their consent by ticking the regarding consent-statement. They also have to fill in their study ID, provided in the invitation letter sent by the GCCR, to identify themselfes. The follow-up survey after one year will also be sent to the participants via the respective centres (as in phase 1). CCS who are interested in LTFU care but refuse to participate in the randomisation trial before they were informed about the randomization result are asked to participate in the pre-post-comparison (phase 1).

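### Phase 2: the covariates named for the primary model leave out the baseline score of the outcome and residency, which forgoes power but does not cause a shortfall

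*Protocol article*

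**What the plan says.** The Statistical analysis section describes the primary model for both phases as "estimating generalized linear models including primary oncological disease, sex, and time since treatment as covariables", and adds: "Details will be fixed in the statistical analysis plan".

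The account of phase 2 under Study design says that the group drawn up by the registry is "stratified according to gender, cancer diagnosis, time since end of therapy and residency". Of the intervention group it says: "They complete the questionnaires web-based before their first visit as well as after 12 months". The waiting control group will "receive an invitation to complete the questionnaires web-based initially and a second time after 12 months".

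The section on ethics approval and consent describes how allocation is disclosed. After the survivor agrees to take part, the centre coordinator "informs the CCS afterwards by email about the randomisation result and a proposed date for the first LTFU appointment". The link to the web questionnaires is described directly after this.

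The phase 2 sample size is set so that "an effect of delta = 0.25 can be detected with a power of 80% for both primary endpoints", which leads to "310 patients per risk group (each in the intervention and control group), i.e. 620 patients in one stratum". If recruitment is too low, one primary endpoint is given up and 255 per arm are planned.

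**The concern.** Three of the four stratification factors return as covariates and the fourth, residency, does not. The baseline value of the outcome is also absent. For a self-report scale measured twice in the same people, that value is usually among the strongest predictors of the later score. Both variables are already collected.

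Two things are at stake. The first is precision: adjusting for a prognostic baseline shrinks the residual variance and corrects for chance imbalance between arms. This matters here because the plan itself foresees low recruitment and would respond by dropping a primary endpoint. The second is agreement between design and analysis: a model that leaves out a stratification factor does not fully reflect how the arms were formed.

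**Working it through.** **Inputs.** From the Statistical analysis section: standardised effect 0.25 (SD = 1), power 80%, 310 per arm for two endpoints, 255 per arm for one. The phase 2 alpha is not stated. I infer 2.5% two-sided per endpoint (5%/2) because it reproduces the planned size. The baseline-to-12-month correlation r and the share of variance explained by residency (R²) are not in the document, so both are assumed and shown as ranges.

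**Reproducing the plan's figures, without baseline.** Normal approximation, n per arm = 2(z₁₋α/₂ + z₀.₈)² / 0.25².
- Two endpoints: 2 × (2.241 + 0.842)² / 0.0625 ≈ 304.2, so 305 per arm, against 310 planned.
- One endpoint, alpha 5%: 2 × (1.960 + 0.842)² / 0.0625 ≈ 251.2, so 252 per arm, against 255 planned.
- Power at 310: Φ(0.25 × √(310/2) − 2.241) = Φ(3.112 − 2.241) = Φ(0.871) ≈ 80.8%.

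Both planned sizes match a comparison that makes no use of the baseline score, and the stated 80% is met.

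**Adding the baseline score.** Covariance adjustment multiplies the outcome variance by 1 − r², so SD becomes √(1 − r²). Effect 0.25, alpha 2.5% two-sided for the first two result columns:

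| Assumed r | Power at 310 per arm | n per arm for 80%, both endpoints | Power at 255 per arm, one endpoint, alpha 5% |
|---|---|---|---|
| 0 | 80.8% | 305 | 80.6% |
| 0.3 | 84.6% | 277 | 84.1% |
| 0.5 | 91.2% | 229 | 90.3% |
| 0.7 | 98.3% | 156 | 97.7% |

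Example for r = 0.5: Φ(3.112/0.866 − 2.241) = Φ(1.353) ≈ 91.2%, and n = 304.2 × 0.75 ≈ 228.1, so 229.

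**Comparison with the fallback.** Both endpoints could be kept at 255 per arm once 304.2 × (1 − r²) ≤ 255, that is r ≥ √(1 − 255/304.2) ≈ 0.40. Below that correlation, baseline adjustment alone does not rescue the second endpoint. Without adjustment, 255 per arm at alpha 2.5% gives about 72%.

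**Adding residency.** With SD = √(1 − R²) and R² from 1% to 5%, power at 310 per arm goes from 80.8% to between 81.2% and 82.9%, a gain of about 0.4 to 2 points.

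**The case against.** The strongest reply is that the list is not closed. It is introduced as what the models include, and the details are deferred to a statistical analysis plan that is not shown. That stands as a limit: the document does not rule out baseline adjustment. But the article chose to name covariates, reproduced three of four stratification factors, and gave sample sizes that match an unadjusted comparison. The deferral leaves room for the fix without supplying it. Nor would bringing the baseline in through change scores be equivalent. The variance factor is then 2(1 − r), and power at 310 per arm would be about 65%, 81% and 96% at r = 0.3, 0.5 and 0.7, never above covariance adjustment.

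Second, the gain rests on an unknown correlation. This also stands. At 0.3 the gain is only about 4 points. For satisfaction the correlation may well be low: the exclusion criteria bar people who already had interdisciplinary follow-up, so the intervention arm rates care at 12 months that it had not received at baseline.

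Third, the baseline may not be a clean pre-allocation measure. Because the questionnaire link is described together with the e-mailed result, some participants may answer knowing their arm. Adjusting for a score that allocation has influenced could introduce bias. This stands and shapes the fix.

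Fourth, leaving a balanced stratification factor out of a linear model generally makes standard errors too large, so the test tends to be conservative. That is correct, and the residency point is minor. Stratification also applies to the invited group before consent, so balance among those who enrol is not guaranteed.

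A reader might also infer that phase 1 is affected: that an unpaired model would lose much of the planned power, or that time since treatment, rising by three years for everyone, would absorb the pre-post effect. The document does not support either. Study design calls phase 1 a pre-post comparison, and n = 370 agrees with a paired calculation (361 by the t-test at two-sided 1.25%, 90% power, delta = 0.2). Nothing describes a stacked unpaired model, and nothing says that time since treatment is updated at follow-up. Taken at inclusion, it leaves the pre-post estimate unaffected.

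**Conclusion.** The point holds for phase 2, as forgone power. The named covariates omit a baseline score that both arms provide and one of four stratification factors, while the stated 80% is met without either (about 81% at 310 per arm). It would be wrong to read this as an underpowered design or an invalid test.

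The size depends on the assumed correlation: about 4, 10 and 17 points of power at 0.3, 0.5 and 0.7. The practical value is greatest if recruitment falls short, since from a correlation of about 0.40 upwards both endpoints could be kept at the size planned for one. Residency belongs in the model for consistency with the design, not for the 0.4 to 2 points it may add. These figures rest on the inferred two-sided alpha of 2.5%, a linear model, and a baseline not influenced by allocation.

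**What to change.** In the statistical analysis plan, specify the phase 2 primary model as a linear model of the 12-month score on arm, baseline score of the same scale, sex, diagnosis group, time since end of therapy and residency. Have the baseline questionnaire completed before the allocation result is sent. Where this cannot be ensured, report the model without the baseline score as a sensitivity analysis. Before any decision to drop a primary endpoint, recompute the required size with baseline adjustment over a stated range of correlations.

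For phase 1, at most one clause is needed: time since treatment is taken at inclusion in the within-patient analysis.

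The analysis change costs only wording, since all variables are already collected. Moving the baseline questionnaire ahead of disclosure requires a change in the order of the centres' contacts with participants.
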